## Abstract

**Introduction::**

Reversible cerebral vasoconstriction syndrome (RCVS) is a rare, but increasingly recognised cerebrovascular condition with an estimated annual age-standardised incidence of approximately three cases per million. Knowledge about risk factors and triggering conditions and information about prognosis and optimal treatment in these patients are limited.

**Methods::**

The REversible cerebral Vasoconstriction syndrome intERnational CollaborativE (REVERCE) project aims to elucidate the epidemiological and clinical characteristics of RCVS by collecting individual patient data from four countries (France, Italy, Taiwan and South Korea) in the setting of a multicentric study. All patients with a diagnosis of definite RCVS will be included. Data on the distribution of risk factors and triggering conditions, imaging data, neurological complications, functional outcome, risk of recurrent vascular events and death and finally the use of specific treatments will be collected. Subgroup analyses will be made based on age, gender, aetiology, ethnicity and geographical region of residence.

**Ethics and dissemination::**

Ethical approval for the REVERCE study will be obtained from national or local institutional review boards in the participating centres. When needed, a standardised data transfer agreement will be provided for participating centres. We plan dissemination of our results in peer-reviewed international scientific journals and through conference presentations. We expect that the results of this unique study will lead to better understanding of clinical and epidemiological characteristics of RCVS patients.

Although vasoconstriction is reversible and the functional outcome reported by most studies is good,^8,19–21^ sequelae from neurological complications might impact the prognosis, with need for a referral to a rehabilitation clinic or nursing home in up to one-third of patients.^
22
^ Furthermore, recurrence of RCVS has been reported.^10,23^ Randomised controlled trials for treatment of RCVS have not been performed so far, and empirical treatment varies between countries. To date, information regarding causative risk factors, aetiology and long-term prognosis is scarce and mainly based on national cohorts. In addition, only few studies have taken ethnicity and geographical region of residence into account.^
24
^

There is a medical need to identify predictors for complications, for a poor functional outcome and for recurrence in order to guide clinical management of patients with RCVS. Given the relatively low incidence of the syndrome, only a multicentre study can provide a sufficiently large sample size to reach adequate statistical power for subgroup comparisons and longitudinal analyses. We therefore launched the REversible cerebral Vasoconstriction syndrome intERnational CollaborativE (REVERCE) project, an international consortium aimed at collecting individual patient data from neurological centres with specific expertise on RCVS.

## Methods and design

### The REVERCE network

REVERCE is an international investigator-driven network of neurological centres with special interest in headache and cerebral vascular disorders in adults, aimed at recruiting patients with RCVS in the setting of a hospital-based, multi-centre, observational study. The international coordinating centre is the University Hospital Montpellier, France. Each participating country has a national coordinating centre. A steering committee will be composed by two designated representatives from each participating country. There is no official chair and no official administration, board or secretary. To date the consortium is composed of referral centres located in the following four countries in Europe and Asia: France (two centres),^8,14,17,25–28^ Italy (28 centres, all referral centres participating in the Italian Project on Stroke at Young Age (IPSYS)),^
7
^ Taiwan (one centre)^2,10,29–32^ and South Korea (one centre)^9,33–37^ (Figure 1, Supplemental Appendix).

**Figure 1. fig1-23969873231182207:**
[figure not shown]
REVERCE recruiting centres. National coordinating centres are labelled with city names, participating centres are indicated in red, and are listed in the Supplemental Appendix.

The REVERCE network welcomes participation and project proposals of further centres. The four national coordinating centres have established the REVERCE network with the first objective to compare characteristics of RCVS between European and Asian patients with data from the four largest European and Asian cohorts to date.^7–10^ In order to participate or suggest a novel project, the REVERCE coordinating centre in Montpellier can be reached via the corresponding author. On request, the standardised data collection form and project proposal form will be forwarded.

### Study aims and hypotheses

The Supplemental Table 1 lists selected intended projects, principal hypotheses and analysis plans.

The overall aim of REVERCE is to perform epidemiological and clinical research on RCVS, investigating risk factors and triggering conditions, pathophysiology, treatment, functional outcome, long-term risk of recurrent events and death, with special emphasis on ethnic and regional variation.

Our first project will be the comparison of patients with RCVS in Asia and Europe. Based on the published literature, we hypothesise that patients in Asia present less often neurological complications of RCVS, and less often secondary forms. If these hypotheses were confirmed with adjustment for selection bias, this could provide relevant insight into pathophysiology and the clinical spectrum of RCVS (subtypes).

Our second project will be the development of a clinical score to predict the risk for neurological complications of RCVS. This score could help clinicians to guide decisions on inpatient or outpatient care, length-of-stay, and use of intra-arterial procedures in severe cases. Based on results from national cohorts, we hypothesise that demographic variables (e.g. female sex, older age), comorbidities (e.g. depression or anxiety), and clinical characteristics (e.g. absence of TCH at onset) predict the risk for neurological complications.

### Patient eligibility

We will identify consecutive patients with ﬁrst-ever RCVS at institutions included in the REVERCE network, which serve as referral centres for neurological diseases in their region. Patients will be recruited both prospectively and retrospectively, according to the local study protocols. Retrospective patients had a qualifying event before the beginning of the study in each centre and will be identified through local registries. RCVS patients are recruited prospectively from the outpatient headache clinic, inpatient consultations, emergency unit, stroke unit or the neurology ward in each centre. Diagnostic criteria are summarised in Supplemental Table 2.

Only patients with definite RCVS according to the consensus criteria^3,4^ are included in the registry, regardless of whether they had neurological complications or not. In patients without (information about) headache, the consensus criteria for RCVS except for the presence of headache must apply, and occurrence of a focal deficit or seizure is necessary to determine the onset of RCVS. In ambiguous cases, the diagnosis must be validated by two members of the steering committee. Patients with probable RCVS, presenting either with headache probably attributed to RCVS according to the third edition of the International Classiﬁcation of Headache Disorders (ICHD-3),^
5
^ or with focal deficits, seizures, or vascular lesions suggestive of RCVS but with normal cerebral angiography do not qualify for inclusion.

### Data collection and storage

Participating centres will transfer their anonymised coded data electronically, according to current laws and legislation at each participating centre, to the REVERCE research team at the Montpellier University Hospital, France. Each participating centre will provide their data by using an encrypted file containing pre-specified variables of interest. The key linking anonymised data at the participating centres. All received data will be entered in a uniform database in IBM SPSS Statistics and stored on secured servers at the coordinating study centre with exclusive access to designated researchers involved in REVERCE. In case of incomplete or implausible data, the REVERCE research team will contact the study investigators to resolve these issues. All data will be processed, stored (for at least 15 years), and destroyed after end of the study according to European Union General Data Protection Regulation.

### Sample size and power calculation

Based on our literature search and consequently estimated available patient data, we aim to include at least 1000 patients for the first analyses, as this size will allow assessing epidemiological characteristics and prognosis of RCVS patients in meaningful subgroups.

### Baseline variables

Data for each individual patient are collected from the hospital at index event or at outpatient clinic evaluation. Baseline data include demographic characteristics, medical history and medication used on admission, potential precipitating and triggering factors, diagnostic workup (i.e. vascular and brain imaging, blood analyses, CSF analyses) and treatment. Cardiovascular risk factors and comorbidities as defined^
38
^ in Supplemental Table 3 will be documented.

### Precipitating factors for RCVS and triggers for headache episodes

We will collect detailed information on precipitating conditions and triggers for headache (Supplemental Table 4). In case of specific precipitating factors with a clear temporal association, RCVS will be qualified as *secondary* or *idiopathic*.^7–11^ A temporal association will generally be considered if the precipitating condition occurred within 4 weeks prior to RCVS onset, with exception for drugs and medications with a longer half-life. Postpartum RCVS mainly occurs during the first month after delivery,^
39
^ but might occur later as previously described for late onset postpartum eclampsia.^
40
^ Therefore, in RCVS occurring later than 4 weeks after delivery, postpartum will be considered as precipitating factor on a case-by-case basis and validated by two members of the steering committee. Remote emotional stress (e.g. serious illness of a family member, work overload) within 4 weeks prior to onset of RCVS will be documented, but not classified as a cause for secondary RCVS. If triggers for headache episodes (e.g. exertion, sexual activity) are reported, but there is no precipitating condition, RCVS is considered idiopathic.

### Clinical features

We will retain data on headache characteristics and any neurological symptoms. In particular, information on duration of symptoms prior to establishment of diagnosis, date of established diagnosis, presence of clinical complications (i.e. transient deficit (aura-like or transient ischaemic attack-like), persistent deficit, and seizure), and treatment will also be collected. At baseline, the severity of stroke (if any) is assessed with the National Institutes of Health Stroke Scale (NIHSS) score^
41
^ and the functional neurological outcome by the modified Ranking Scale (mRS).^
42
^

### Neuroimaging

At all centres, patients with suspected RCVS undergo cerebrovascular imaging (CTA, MRA or conventional cerebral angiography) and cerebral imaging (CT, MRI) applying the respective local imaging protocols. According to the consensus criteria for diagnosis of RCVS, cerebrovascular imaging is performed at least once at onset to confirm cerebral vasoconstriction with ⩾2 narrowing on two different arteries, and once at 3 months follow-up to confirm reversibility of vasoconstriction. Cerebral imaging is performed at onset and is repeated in case of clinical worsening. MRI sequences at all centres include at least DWI, ADC, FLAIR and T2* or SWI, respectively.

Cerebrovascular imaging will be assessed for (1) the presence of vasoconstriction on ⩾2 different arteries at onset, (2) the presence of concomitant cervical artery dissection, (3) the reversibility of vasoconstriction at 3 months follow-up.

Cerebral imaging will be evaluated for lesions considered as complications of RCVS, namely (1) ischaemic stroke (IS), (2) intracranial haemorrhage (intracerebral haemorrhage (ICH), subarachnoid haemorrhage (SAH), subdural haematoma (SDH)), and (3) PRES. We will document the delay from onset of symptoms to detection of radiological lesions.

These data will be provided by each centre, and will serve for analyses on the presence of the above-mentioned types of lesions.

For further in-depth analyses of radiological lesions, for example, location and size of lesions, we will establish a joint imaging database enabling for central qualitative reading of images following a standardised, structured protocol by experienced neuroradiologists or neurologists, who will be blinded to clinical data.

### Outcome

For retrospectively recruited patients, at least one follow-up at 3 months including proof of reversibility of headache and vasoconstriction is required. For prospectively recruited patients, follow-up evaluations are conducted systematically at 3 months for confirmation of the diagnosis, and subsequently according to the local study protocol. Primary outcomes measures will be the functional neurological status (mRS at 3 months), death and RCVS recurrence. As secondary outcomes for prospectively recruited patients, we will assess quality of life (European Quality of Life 5 Dimensions 5 Level Version, EQ-5D-5L),^
43
^ cognitive function (Montreal Cognitive Assessment, MoCA test),^
44
^ and emotional stress (Depression Anxiety Stress Scale, DASS-21)^
45
^ at 3 and 12 months follow-up.

### Current status of recruitment

For the first analyses from this network, patients recruited retrospectively and prospectively at the participating centres between September 2000 and February 2023 will be included. Currently, data on approximately 800 RCVS patients are available (≈35% of patients recruited from French centres, ≈10% from Italian, ≈40% from Taiwanese, and ≈15% from Korean centres, respectively).

### Lead of distinct project, authorship criteria and dissemination

The researcher(s) who would like to carry out a sub-project in the setting of the REVERCE network shall fill out a standardised project proposal form, which will then be reviewed and approved by the steering committee on the criteria of feasibility, scientific quality and a balanced attribution of sub-projects among the contributing centres. The researcher(s) who put forward the proposal take(s) the lead and will get first and senior authorships. Co-authorships are attributed taking into account all aspects important for the success of a research project. Study results will be published in peer-reviewed journals and be communicated to neurological communities by participating authors.

### Ethical considerations

At the coordinating centre, the University Hospital Montpellier, France, study approval for REVERCE was obtained from the local ethics committees (registration number IRB-MTP_2021_02_202100734). Each participating centre is responsible to obtain local ethics committee approval to collect and pool anonymised data with other centres, to fulfil local, regional and national legal and ethical requirements and to keep a local patient identifier.

### Statistical analysis

The statistical analysis plan specific to projects 1 and 2 is detailed in the Supplemental Table 1. We aim to perform statistical analyses with IBM SPSS Statistics or R (most recent versions). A *p* value of <0.05 with correction for multiple testing when appropriate and/or a 95% CI not containing the value 1 will be considered statistically significant. Differences between groups will be compared using ANOVA test, Student’s *t*-test for continuous variables and χ^
2
^ test for categorical variables. Univariate and multivariable logistic regression analysis will be performed for comparison between groups. In case of missing data at baseline, and if considered necessary, multiple imputation will be used. The cumulative risk of death and outcome events will be assessed with Kaplan–Meier survival analysis, and differences in survival between different subgroups by Log-Rank tests. We will use Cox regression models to obtain HRs and their corresponding 95% CIs to calculate the risk of death and outcome events while adjusting for confounders. Only patients for whom follow-up data is available will be included for these analyses, and patients who have died or were lost to follow-up will be censored from the last available follow-up.

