## Discussion

REVERCE aims to investigate the epidemiological and clinical aspects of RCVS, including risk factors and triggering conditions, to determine functional outcome and the risk of new or recurrent vascular events, and to study disease variation according to geographical region, continent, and ethnicity. The most important strength of our study is the participation of neurological centres from different countries and continents. REVERCE will be the largest study on RCVS with individual data sets ever conducted, with more than 800 patients already included. This large set of data provides sufficient statistical power to not only reliably quantify the differences in risk factors and precipitating conditions between men and women, different age groups, ethnic subgroups and possibly search for differences between region of residence, but also assess the risk of recurrent vascular events. The inclusion of highly phenotyped cases, the high level of completeness of data and the standardised data ascertainment are strengths of REVERCE.

Limitations include the risk of misclassification of risk factors and events of interest during follow-up, since retrospectively recruited patients’ data have been collected according to various not completely identical local protocols. We will harmonise variables across studies as much as possible. Since local registries were set up prior to REVERCE, they did not include all variables, which might implicate a risk of missing data. Furthermore, our study will cover a long time period in which data collection took place, possibly involving variability in the diagnostic workup because of differences in brain imaging protocols and improvements in imaging techniques.

In conclusion, REVERCE will provide sufficient patient numbers to allow for detailed description of the global distribution of risk factors and triggering conditions, and for the quantification of the cumulative risk of outcomes of patients with RCVS. The research protocol explicitly reaches out to other researchers and aims to become a platform that facilitates future collaborative research in the area of RCVS.

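### The single censoring rule for the time-to-event analyses censors patients who die and makes no exception for the analysis of death, a primary outcome

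*Protocol article*

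**What the plan says.** The Outcome section of the protocol article lists three primary outcomes: "Primary outcomes measures will be the functional neurological status (mRS at 3 months), death and RCVS recurrence".

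The Statistical analysis section then sets out the time-to-event methods. Absolute risk: "The cumulative risk of death and outcome events will be assessed with Kaplan–Meier survival analysis". Subgroups are compared by log-rank tests. Regression: "We will use Cox regression models to obtain HRs and their corresponding 95% CIs to calculate the risk of death and outcome events".

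One sentence then governs all of this. Its first half fixes the analysis set: "Only patients for whom follow-up data is available will be included for these analyses". Its second half fixes censoring: "patients who have died or were lost to follow-up will be censored from the last available follow-up". It does not separate the analysis in which death is the endpoint from those in which it is not.

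The Discussion names the product that depends on these methods: the study is to provide enough patients "for the quantification of the cumulative risk of outcomes of patients with RCVS".

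**The concern.** A censored patient contributes time at risk but no event. If patients who die are censored, they cannot be counted as deaths, yet death is the first endpoint named for the Kaplan–Meier and Cox analyses. As written, the rule removes every event from the analysis of a primary outcome.

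There is a lesser consequence for recurrence. Censoring at death makes one minus Kaplan–Meier estimate the recurrence risk that would apply if nobody died. That is at or above the proportion of patients who actually have a recurrence, which is what a reader takes a cumulative risk to mean.

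The network is open to new centres and sub-project leads, so the written rule may be applied by analysts who did not draft it.

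**Working it through.** The article gives no mortality, recurrence rate or event count for the study, so there is no figure of its own to reproduce. The death result needs no numerical assumption. The recurrence result needs an assumed range.

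**1. Death under the literal rule.** Set the event indicator to 0 for every patient who dies.

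- Kaplan–Meier: S(t) is the product, over event times, of (1 − events / number at risk). With no event times S(t) = 1, so the risk of death is 1 − 1 = 0% at all t.
- Log-rank: observed minus expected events is 0 in every group and its variance is 0, so the statistic is 0/0.
- Cox: the partial likelihood has one term per event. With none it is flat, and no hazard ratio exists.

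An illustration used 1000 simulated patients, the planned minimum ("we aim to include at least 1000 patients for the first analyses"), a 5-year horizon and staggered censoring, with one dataset per row:

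| Assumed true 5-year mortality | Deaths observed | Kaplan–Meier risk, death as event | Kaplan–Meier risk, literal rule |
|---|---|---|---|
| 1% | 6 | 0.8% | 0.0% |
| 2% | 16 | 2.1% | 0.0% |
| 5% | 35 | 4.5% | 0.0% |

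**2. Recurrence with deaths censored.** Assume constant cause-specific hazards, with cumulative hazards Lr (recurrence) and Ld (death) over 5 years.

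- One minus Kaplan–Meier: 1 − exp(−Lr).
- Cumulative incidence with death competing: Lr/(Lr + Ld) × [1 − exp(−(Lr + Ld))].

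Worked case, recurrence 10% and mortality 5%: Lr = −ln 0.90 = 0.1054 and Ld = −ln 0.95 = 0.0513. Cumulative incidence = 0.1054/0.1567 × (1 − 0.90 × 0.95) = 0.6726 × 0.145 = 9.75%. The excess is 10.00 − 9.75 = 0.25 percentage points, a ratio of 1.025.

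| Assumed 5-year mortality | True incidence when 1 − KM is 5.00% | True incidence when 1 − KM is 10.00% | Largest excess (percentage points) | Relative excess |
|---|---|---|---|---|
| 1% | 4.98% | 9.95% | 0.05 | about 0.5% |
| 2% | 4.95% | 9.90% | 0.10 | about 1% |
| 5% | 4.88% | 9.75% | 0.25 | about 2.5% |
| 10% | 4.75% | 9.50% | 0.50 | about 5% |
| 20% | 4.49% | 8.98% | 1.02 | about 11% |

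**3. Comparisons of recurrence.** A Cox model that censors deaths estimates the cause-specific hazard ratio, and the log-rank test compares cause-specific hazards. Neither is distorted by the mechanism in step 2, which affects only the absolute risk.

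**The case against.** The strongest reply is that nobody would apply the rule literally. The same section twice names death as an endpoint, so an analyst following it would have to code death as an event. The clause is probably the usual rule for non-fatal outcomes, attached to both by careless drafting. A Cox model with no events would also fail visibly, not produce a misleading estimate. This is plausible, and a reader should not infer that the study will publish a mortality of zero. The point that stands is that the text gives one rule for all these analyses, states no exception, and contradicts the purpose of one of them.

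A second reply is that such detail belongs in a fuller analysis plan. That holds for the choice of a competing-risk method: not naming one in an article is no error. It does not hold for the death analysis, where the article fixes a rule and the rule is wrong. The supplementary table it cites for analysis detail is described as specific to the first two projects, the Asia–Europe comparison and the complication score. The hypotheses stated for those projects do not rest on this rule.

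A third reply is that the recurrence effect is nearly immaterial. This largely stands. The Introduction describes functional outcome as good in most studies. Retrospective patients must also have a 3-month follow-up showing reversibility, which makes early deaths unlikely among them.

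**Conclusion.** The concern holds for the analysis of death. On its literal wording the rule leaves a primary outcome with 0 events, a Kaplan–Meier risk of 0%, and no estimable log-rank test or hazard ratio. This rests only on the text and the definition of censoring.

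For recurrence the direction is certain whenever a patient dies before recurring, but the size is small: about 0.3 percentage points or less at mortality up to 5%, for recurrence of 5% to 10% over 5 years with constant hazards. These inputs are assumptions.

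A reader might infer that the rule also biases the subgroup contrasts, most of all in high-mortality groups such as patients with haemorrhage or large infarcts. The documents do not support this. Log-rank and Cox comparisons of recurrence remain valid as cause-specific comparisons. The subgroups listed in the abstract are age, gender, aetiology, ethnicity and region, and no mortality is given for any of them.

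**What to change.** Replace the censoring clause with wording such as:

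> In the analysis of death, death from any cause is the event, dated at death, and patients alive are censored at last contact. For recurrence and other non-fatal events, cumulative risk is estimated by the cumulative incidence function (Aalen–Johansen) with death as a competing event; cause-specific Cox models censor patients at the date of death or at last contact.

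The text should not also say that only living, event-free patients are censored, because the cause-specific Cox model for recurrence does censor at death. Using the date of death also keeps follow-up time that is lost when a patient who died is cut off at an earlier visit.

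The cost is one reworded clause, minor extra analysis in R, which the plan already names, and use of the date of death. Sample size and design do not change.
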